### Recruitment

Patients will follow the department’s normal procedure in terms of in situ bypass. They will then be asked in the outpatient’s clinic during a visit to prepare for the operation.

### Assignment of Intervention

#### Allocation

Allocation will be by randomization.

#### Sequence generation

The study will use an online randomization program. The total distribution between the two groups is 1:1, but a block randomizing will be used in different sizes.

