## Introduction

Critical leg ischemia (CLI) is a predominant cause of poor wound healing, leg amputation [1], and has a significant, negative impact on quality of life [2]. In patients with CLI, the standard operative choice is an in situ bypass to the lower extremity to improve the patient's prognosis and quality of life. However, postoperative complications after an in situ bypass occur in 18% of patients, prolonging their hospitalization and convalescence. The main postoperative complication is edema. Measured 10 cm below the patella, edema is developed among approximately 6%-8% during the first day, increasing to 8%-10% at the fourth day (nonpublished). Postoperative edema can be prevented by early mobilization which stimulates the natural venous pump in the leg, but mobilization is often difficult in patients with CLI due to wound problems prior to surgery. In addition, CLI is associated with age and limited walking distance and coexists with other manifest diseases, which might also make mobilization difficult. Supportive stimulation of the venous pump by an impulsive compression foot pump may be an effective solution. Patient’s stimulation of the venous plexus in the arch of the foot has shown to reduce leg edema and thrombosis risk in patients undergoing orthopedic surgery on the lower extremities [3-10]. However, in the literature, there is no description of treatment of vascular surgical patients treated with foot pump. Thus, the primary objective of this study is to investigate whether a foot pump is effective in reducing postoperative edema in patients undergoing an in situ bypass.

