### Background and Rationale

In situ bypass to the lower extremity is the standard operation choice on patients with critical leg ischemia, accounting for approximately 18% of patients’ wound problems [11], prolonging their hospitalization time and convalescence. One of the reasons for wound problems is postoperative edemaThe edema is expected after open vascular reconstruction (in situ bypass surgery). Early mobilization can prevent development of the postoperative edema. Through mobilization, the patient stimulates the natural venous pump in the leg. However, patients are often hard to mobilize in an early stage due to the wound and age. Stimulation of the venous plexus in the arch of the foot has, in other categories of patients, shown to reduce postoperative edema of leg and thrombosis risk in patients undergoing orthopedic surgery on the lower extremities. The subjective quality of life is often impaired in relation to the above mentioned surgical treatment. Through a quicker recovery, the patient can rapidly regain mobility and walking capability.

There is no analysis or meta Cochrane reviews in this field.

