### Participants, Interventions, and Outcomes

#### Eligibility criteria

##### Inclusion:

The study will include patients who have undergone in situ from common femoral artery to a popliteal artery above knee/below knee or crural artery.

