#### Allocation concealment

#### Mechanism

Last minute randomization will occur at onset of surgery by study coordinator.

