### Statistical methods

Descriptive statistics will be used to report study results. For binary and categorical variables, tests of differences between the intervention and control group will be analyzed by the chi-square test. For continuous variables, initial tests will be performed to check for normality of data by using histograms, Q-Q plots and the Shapiro-Wilk test. Normally and nonnormally distributed variables will be analyzed by *t* test or the Wilcoxon rank sum test, respectively. *P* values <.05 will be considered statistically significant.

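### All planned comparisons are unadjusted although the protocol itself names pre-operative wounds and age as hindering mobilisation: a small, cheap gain in precision is left unused

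*Protocol article*

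**What the plan says.** The tests are fixed in the protocol article under Statistical methods. For binary and categorical variables, "tests of differences between the intervention and control group will be analyzed by the chi-square test". Continuous variables go, according to a normality check, to a t "test or the Wilcoxon rank sum test, respectively". No covariate enters any comparison.

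Two earlier sections describe what delays recovery. The Introduction says "mobilization is often difficult in patients with CLI due to wound problems prior to surgery". Background and Rationale says "patients are often hard to mobilize in an early stage due to the wound and age", and also "Early mobilization can prevent development of the postoperative edema". Under Outcomes, time to mobilisation is itself an endpoint, next to leg edema, wound complications and length of stay.

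On allocation, Sequence generation says "The total distribution between the two groups is 1:1, but a block randomizing will be used in different sizes". On timing, the Mechanism paragraph says "Last minute randomization will occur at onset of surgery by study coordinator". Age and existing wounds can therefore be known before the arm is assigned.

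**The concern.** By the protocol's own account, wounds and age affect how soon a patient is mobilised, and mobilisation affects edema. For time to mobilisation the link is direct; for edema it runs through mobilisation. Both features should vary among the enrolled patients. The age range is 18 to 99. Only wounds that rule out foot compression are excluded, and healing of ischemic ulcers is among the objectives.

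If these features predict the outcome, a two-group test leaves the variation they explain in the error term, so the confidence interval is wider than it need be. In a trial of 100 patients that is worth avoiding when the remedy is a few lines of text. The covariates also have to be named in advance: the trial is unblinded once the operation ends, and covariates chosen after the data are seen would be open to challenge.

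**Working it through.** **1. Inputs.** The Statistical Analysis and Structural Analysis section gives a fall from 18% to 12% (6 points), sigma 10, a two-sided alpha of 0.05, 0.80 stated as beta (read here as power), 44 per group, and 6 dropouts per group, making 50. The share of outcome variance explained by age and wound status (R²) is not given. It is assumed below, over a range.

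**2. The plan's own figure.** As a comparison of means, n per arm = 2 × (1.960 + 0.842)² × 10² / 6² = 43.6, rounded up to 44. Adding 6 gives 50. The stated figure is reproduced.

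**3. Effect of adjustment.** In a linear model the residual SD becomes 10 × √(1 − R²). With 44 analysed per arm and the normal approximation, power = Φ(6 / (residual SD × √(2/44)) − 1.96).

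| Assumed R² | Residual SD | Power, 44 per arm | n per arm for 80% power |
|---|---|---|---|
| 0 (as planned) | 10.00 | 80.4% | 44 |
| 0.05 | 9.75 | 82.3% | 42 |
| 0.10 | 9.49 | 84.3% | 40 |
| 0.20 | 8.94 | 88.2% | 35 |

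**4. Which R² is plausible.** Suppose a binary factor with prevalence p shifts the outcome by 5 points (assumption: half the SD). It then explains R² = p(1 − p) × 5² / 10², which is 0.0525 at p = 0.3 and 0.0625 at p = 0.5. One such factor is worth about 2 points of power. An R² of 0.20 would need three to four independent factors of that strength, so with two covariates the lower rows of the table are the optimistic ones.

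**5. Chance imbalance.** At 50 per arm, a binary factor differs between arms by 10 points or more in 34% of trials at prevalence 33%, and in 37% at prevalence 50% (exact binomial). A difference of 20 points or more occurs in 4.3% and 5.7%. With the assumed 5-point effect, an imbalance of 15 to 20 points moves the estimate by 5 × 0.15 = 0.75 to 5 × 0.20 = 1.0. The standard error of the difference is 10 × √(2/50) = 2.0, so even this uncommon imbalance moves the estimate by at most half a standard error.

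**6. Wound complications.** The plan's rates give 50 × 0.18 + 50 × 0.12 = 9 + 6 = 15 events, and fewer in each part once groin and leg wounds are separated as the endpoint requires. A logistic model with arm, age and wound status would have 15 / 3 = 5 events per coefficient at best.

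**The case against.** The strongest reply is that nothing here is an error. Blocked 1:1 randomisation followed by t, Wilcoxon or chi-square tests is a valid analysis. That stands in full. A reader might infer that chance imbalance in wounds or age would bias the comparison. It would not: imbalance of this kind is part of the sampling variation that the standard error already covers, and alpha is not inflated.

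A reader might also infer from Sequence generation that randomisation is unstratified. The text names no stratification factor, but it rules none out, and a condensed article may leave strata to the full protocol. Stratification is in any case a trade-off with 100 patients, so no change to the randomisation is argued for.

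A third tempting step is to count graft level as known prognostic information, because the eligible bypasses run from the "common femoral artery to a popliteal artery above knee/below knee or crural artery". The documents list these targets for eligibility and nowhere link them to edema, mobilisation or wounds.

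Three further objections limit the size of the point:

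- The statements on wounds and age describe these patients as a group, and they reach edema only through mobilisation.
- Sigma 10 stands in a sentence about wound complications, so using it as the SD of swelling is an assumption.
- Baseline circumference, which is measured at inclusion, may well predict later circumference better than either factor. Analysing change already uses it in part, and what wounds and age add could be small.

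The objection does not remove the core. The unadjusted tests are a stated choice, and the protocol itself names two features that bear on its endpoints.

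**Conclusion.** The point holds as an efficiency suggestion of low severity. The stated analysis is sound, and what it forgoes is precision. On the plan's own inputs the gain is about 2 points of power at an assumed R² of 0.05, 4 at 0.10 and 8 at 0.20, and step 4 of the working makes the low end the more likely. No firmer figure can be given, because the documents contain no R² for age or wounds and no SD stated for edema itself.

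The gain applies to the continuous outcomes. The reduction in residual variance is a linear-model result and does not carry over to logistic regression, where adjustment also changes the odds ratio being estimated.

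Nor should adjustment be read as a repair of the sample size. If 18% versus 12% is treated as two proportions, 555 per arm are needed and 44 per arm give about 12% power. That is a separate and much larger matter.

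**What to change.** In Statistical methods:

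- **Leg edema:** make the main comparison a linear regression of change in circumference on arm, with age and pre-operative foot wound (yes/no) as pre-specified covariates. Report the adjusted difference with its 95% CI.
- **Time to mobilisation:** adjust for the same two covariates, and name the model in advance.
- **Sensitivity analysis:** keep the planned unadjusted tests for both outcomes.
- **Wound complications:** leave unadjusted.

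The cost is a few lines of text and two degrees of freedom (88 analysed patients: 86 residual degrees of freedom unadjusted, 84 adjusted). Baseline wound status must also be entered on the data sheet, since the article's measurement schedule does not list it. No extra patients and no change to the randomisation are needed.

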#### Allocation concealment

#### Mechanism

Last minute randomization will occur at onset of surgery by study coordinator.

### Implementation

#### Informed consent

Patients with critical leg ischemia that are being assessed for inset bypass will be offered to participate in the trial by ambulatory visit. There will be a sheet with written information handed out and the patients will also receive oral information about the trial. The patient then has the option for consideration until the randomization happens at admission to operation. The oral information will be given by the research nurse and study physician through a phone call from a study room in the outpatient clinic at Department of Vascular Surgery, Lillebaelt Hospital, Denmark. The patient is then given the written information to take home for reading and can have an observer present at the hospital where the patient must submit a statement of participation in the study. The time between ambulatory visit and hospitalization will usually be 7 to 14 days, depending on the severity of the patient’s ischemia.

### Blinding

Patient and surgeon will be blinded to the allocation during surgery but will need to be unblinded at the time when the intervention is initiated immediately after surgery.

### Data Collection, Management, and Analysis

#### Data Collection Methods

##### Data Application Sheet

A data application sheet will be created for all the included patients. The information will be fed into the database for analysis.

#### Data management

Data management will be handled in the Data Analysis and Statistical Software program (STATA version 13). A special data applications model has been constructed for the study in Open (Odense Patient Data Explorative Network).

### Statistical methods

Descriptive statistics will be used to report study results. For binary and categorical variables, tests of differences between the intervention and control group will be analyzed by the chi-square test. For continuous variables, initial tests will be performed to check for normality of data by using histograms, Q-Q plots and the Shapiro-Wilk test. Normally and nonnormally distributed variables will be analyzed by *t* test or the Wilcoxon rank sum test, respectively. *P* values <.05 will be considered statistically significant.

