**Methods:**

The protocol is designed as a randomized, unblinded prospective study with 50 patients in each group. Standard postoperative routines after bypass surgery, including short-stretch bandaging of the operated legs, are compared to supportive stimulation of the venous pump by an impulsive compression foot pump. The postoperative edema of the leg is measured 10 cm below the patella and 8 cm proximal to the medial malleolus. Measurements are performed preoperatively, 1 and 4 days postoperatively and at discharge.

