**Results:**

The primary endpoint is reduction of leg edema by at least 50%. The secondary endpoint includes earlier mobilization in the pump group and decreased length of stay in hospital. Quality of life is evaluated through the European Health Related Quality of Life Questionnaire 5 Dimensions (EQ-5D) and Vascular Quality of Life Questionnaire-6 (VascuQol-6) questionnaires. The start of the study is February 1, 2018, and the end of the study is February 1, 2020. First results will be available April 2020.

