#### Time Schedule for Measuring Assessing Symptoms As Edema

The time schedule will be as follows:

In the open clinic when the patient is included.The day after the operation.Day 4 and the day of patient discharge.Day 42 (control in our open clinic for control of the operation results).

The measure procedure will be as follows:

The circumference of the leg will be measured at 10 cm below the distal part of the patellae and 8 cm above medial malleolus.In the same procedure, we will evaluate pain by the Visual Analogue Scale (VAS).Randomization when the patient is on the operation table.Operation performed.Post operation.The control group follows the department’s ordinary postoperative routines for inset bypass — short-stretch bandage. A short-stretch bandage is a padded bandage that stretches from the toes and up to the upper thigh with a 40 mmHg pressure.Time for full mobilization is recorded in all patients.Reoperations is noted.Toe pressure is measured at inclusion, immediately post operation and at discharge.Time for discharge is noted.Paraclinical factors to be examined: confusion, pneumonia, infection of the urinary tract.Duplex study at Day 42 of reverse flow in the deep veins associated with standard duplex study of AV fistulas postoperatively.Quality of life questionnaire (VascuQol-6) baseline + 42 days + 6-month + 12-month, (Appendix 1).EQ-5D baseline + 42 days + 6-month + 12-month, (Appendix 2).

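### For continuous outcomes the test is picked by a normality check on the trial's own data, and no adjustment for the preoperative circumference is specified

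*Protocol article*

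**What the plan says.** The Statistical methods section of the protocol article is the only analysis text, and its rules are general. Binary and categorical variables get a chi-square test. For continuous variables, "initial tests will be performed to check for normality of data by using histograms, Q-Q plots and the Shapiro-Wilk test". Then: "Normally and nonnormally distributed variables will be analyzed by *t* test or the Wilcoxon rank sum test, respectively". The section does not say how the three checks are combined or what result counts as non-normal. It names no covariate and makes no exception for the primary endpoint.

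A baseline value is available. The abstract's Methods state: "Measurements are performed preoperatively, 1 and 4 days postoperatively and at discharge". The time schedule places the first measurement at the outpatient visit ("In the open clinic when the patient is included") and describes the variable: "The circumference of the leg will be measured at 10 cm below the distal part of the patellae and 8 cm above medial malleolus".

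The endpoint is worded in terms of edema, not circumference. The abstract has "The primary endpoint is reduction of leg edema by at least 50" percent. The End points section describes a 50% reduction at both sites, three days after surgery, relative to untreated patients. Neither place gives a formula that turns circumferences into edema.

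**The concern.** Two things are fixed badly if edema is a continuous outcome.

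First, the t test and the Wilcoxon test address different quantities. A halving of edema between groups is most naturally a statement about means. The rank sum test does not estimate a mean difference. Letting a normality check choose between them means that the quantity being compared is settled only after the outcome data have been seen.

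Second, edema is by nature a rise over the patient's own preoperative size, and that size is recorded. Neither two-group test takes it in as a covariate. Whether this loses anything depends on how the edema variable is built and on how the rise relates to leg size, so the size of the loss has to be worked out.

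**Working it through.** **The plan's own figure.** The Statistical Analysis and Structural Analysis section gives a difference of 18 − 12 = 6, sigma 10, two-sided alpha 0.05 and 0.80 (printed as beta, read as power). The formula for an unadjusted comparison of two means is n = 2(1.960 + 0.842)² × 10² / 6² = 43.6, so 44 per arm, as stated. The plan is therefore sized on a comparison of means with no covariate. (Using a means formula for complication rates is a separate matter.) I use 44 evaluable patients per arm below.

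**Pretest: error rate.** Simulation with 44 per arm and 20,000 trials per distribution. Shapiro-Wilk was applied at 0.05 in each arm, with Wilcoxon used if either arm failed. That threshold is my assumption, since the plan gives none. Both arms were drawn from the same distribution.

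| Distribution | Wilcoxon chosen | Type I error of the whole procedure |
|---|---|---|
| Normal | 10% | 0.051 |
| t, 4 df | 68% | 0.048 |
| Gamma, shape 4 | 86% | 0.051 |
| Lognormal (log SD 0.5) | 99% | 0.052 |
| Exponential | 100% | 0.050 |

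There is no material inflation. The test used does vary, from mostly t to almost always Wilcoxon.

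**Pretest: what is tested.** Both arms were given the same mean but different shapes (gamma 4 against gamma 1.5, 10,000 trials). The t test rejected in 5.7%, Wilcoxon in 16.7% and the pretest procedure in 16.7%, because it chose Wilcoxon in 99% of trials. The shapes were picked to show the mechanism: a significant result can then reflect a difference in shape with no difference in mean edema.

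**Baseline adjustment: assumptions.** The documents do not give these inputs: preoperative calf mean 35 cm with SD 3 to 4 cm, and SD of percent rise 6, 8 or 10 points. The control rise of 9% is the middle of the Introduction's 8%-10% at day 4, read as percent rise. Halving it gives a difference of 4.5 points.

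Unadjusted t test on percent rise, normal approximation: power = Φ(4.5 / (SD × √(2/44)) − 1.96), with √(2/44) = 0.2132.
- SD 6: 3.52 − 1.96 = 1.56, power 94%
- SD 8: 2.64 − 1.96 = 0.68, power 75%
- SD 10: 2.11 − 1.96 = 0.15, power 56%

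The t distribution gives 94%, 74% and 55%.

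Simulated power of the baseline-adjusted model when the rise is unrelated to leg size (1,500 trials per scenario): 93%, 73% and 56%. Adjustment gains nothing here.

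When the rise falls by 4 points per baseline SD (assumed) and the SD of rise is 8, the t test on percent change has 73% to 74% power and the adjusted model 84% to 85%. That is a gain of about 10 points.

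A t test on raw day-4 circumference, with the rise unrelated to leg size, would have 34-50%, 30-42% and 29-34% power at SD 6, 8 and 10.

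**Cross-check by formula.** With equal SDs before and after surgery and pre-post correlation ρ (assumed), the variance relative to a test of the postoperative value is 1 − ρ² for the adjusted model and 2(1 − ρ) for a change score. Their ratio is (1 + ρ)/2, so adjustment saves 35%, 25%, 15% and 5% of the variance of a change score at ρ = 0.3, 0.5, 0.7 and 0.9. Equal SDs with ρ below 1 imply that larger legs rise less, so this agrees with the simulation: the gain over change scores needs a rise that depends on baseline.

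**The case against.** The strongest reply is that the plan never says raw postoperative circumference is tested. The endpoint is edema, and a 50% reduction makes no sense for leg girth. If edema is computed as percent rise, an unadjusted test already uses the preoperative value, is valid under randomization, and in the main scenario has the same power as the adjusted model. All of that stands. A reader might infer that the plan discards the baseline measurement and gives up half its power. The documents do not support that, because the large contrast appears only against an analysis they do not state.

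A reader might also infer that the pretest inflates the false-positive rate. Under identical distributions it does not, and the 16.7% figure needs arms that differ in shape.

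Two further replies stand in part. The abstract's endpoint can be read as a binary response, which would go to the chi-square test, so that neither criticism would reach it. And an article commonly leaves covariates and derived variables to a fuller document, so the missing edema formula is not itself the fault. The data-driven choice of test is different: the article states it as the rule for all continuous variables, and a later plan would have to contradict it.

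**Conclusion.** The point holds in a limited form. As written, a continuous edema outcome would be analysed by whichever of two tests a normality check with no stated threshold selects, so the target can shift from a mean difference to a rank contrast after the data are seen. No baseline adjustment is specified although the measurement is planned. The gain from adjusting ranges from nothing over a t test on percent change (rise unrelated to leg size) to about 10 power points (assumed slope of 4 points per baseline SD, SD of rise 8). It would be much larger only against raw values. These sizes rest on assumed leg dimensions, SDs and slope, and on reading the Introduction's percentages as percent rise when they could mean a share of patients. The unadjusted tests are valid, and type I error is not at issue under identical distributions. This is a worthwhile improvement at almost no cost, and it does not apply to a binary 50% endpoint.

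**What to change.** For the primary edema endpoint, replace the general rule with one prespecified analysis:

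- A linear model of postoperative circumference on arm and preoperative circumference. The log scale is one option, and then gives the arm effect as a ratio. Report the effect with a 95% CI.
- One named time point. The End points section says three days after surgery, while the abstract and the time schedule have measurements on days 1 and 4. These need to be reconciled.
- A stated role for the two measuring sites, for example which one is primary.
- No normality pretest for this endpoint. Keep a Wilcoxon test on percent change as a sensitivity analysis.
- A sentence saying whether the 50% figure is a contrast between groups or a response within a patient. If it is the latter, the endpoint is binary and the model above does not apply to it.

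The cost is a few lines of wording and one regression in Stata, the software already named. No extra patients, visits or measurements are needed. The change should be made before outcome data are examined by arm.

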### Objectives

The objectives will be as follows:

To investigate whether compression therapy with foot pump reduces postoperative edema.Through reducing edema, facilitate wound healing of the operation wounds, promote healing of ischemic ulcers, and decrease major amputation rate.Shorten hospitalization.Increase and improve the patient’s subjective quality of life faster.

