### Statistical Analysis and Structural Analysis

Through decreasing the postoperative edema by 50 %, we can reduce the wound complication rate for patients from 18% to 12%, given a sigma of 10 and the two-sided test, with an alpha value of 0.05 and beta of 0.80 involving 44 patients in each group. Assuming a dropout rate of 6 patients in each group, the “sample size” will rise to 50 in each group.

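### Quality of life is scored at baseline and three follow-up visits, but the only stated test for continuous variables takes one value per patient and uses neither the baseline nor the other visits

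*Protocol article*

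**What the plan says.** Under Time Schedule for Measuring Assessing Symptoms As Edema, the protocol article lists "Quality of life questionnaire (VascuQol-6) baseline + 42 days + 6-month + 12-month" and "EQ-5D baseline + 42 days + 6-month + 12-month". Each patient is therefore due to give one baseline and three follow-up values on each questionnaire.

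The last item under Objectives is "Increase and improve the patient’s subjective quality of life faster". The Results part of the abstract says that quality of life is evaluated with these two questionnaires. The list under End points (edema, wound complications, time to mobilization, length of stay) does not include it.

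Statistical methods gives one rule by type of variable. For binary and categorical variables, "tests of differences between the intervention and control group will be analyzed by the chi-square test". For continuous variables, normality is checked first, and the comparison is then by t "test or the Wilcoxon rank sum test, respectively". The section names no visit, change score, summary over visits, baseline adjustment or repeated-measures model.

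**The concern.** A two-sample t or rank sum test needs exactly one number per patient. If that number is the score at one visit, the test leaves out two kinds of information already in hand. One is the patient's baseline score, which usually predicts later scores. The other is the set of earlier follow-up scores from patients who lack the form at the visit being tested. It also gives no direct comparison of the course over time, although the objective is about the speed of improvement.

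At stake is the precision and clarity of a stated objective in a trial of 50 patients per arm. The primary edema comparison is not touched.

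**Working it through.** **The plan's own figures.** No sample size is given for quality of life. Statistical Analysis and Structural Analysis has 44 per group. This reproduces as 2 × (1.96 + 0.84)² × 10² / 6² = 43.6, rounded up to 44, with a difference of 6 and a sigma of 10. Adding 6 dropouts gives 50, so the planned loss is 6/50 = 12%. Only the 50 and the 12% are used below.

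**Assumptions.** The article gives no correlation between visits. I assume an equal correlation ρ of 0.5 to 0.7 between any two of the four scores, equal variances, and forms missing at random. Each ratio is the variance of the 12-month arm difference in a repeated-measures model with free arm-by-visit means, divided by 2/n for the two-sample test in the n patients per arm who have a 12-month form. Where baseline is used, its mean is common to both arms.

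**Complete data.**
- Without baseline the ratio is 1.00. The model gains nothing at a single visit.
- With baseline it is 1 − ρ², which is 0.75 at ρ = 0.5 and 0.51 at ρ = 0.7. This holds equally at day 42.

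**Planned 12% loss.** Per arm, 44 patients have all three forms, 3 are lost after 6 months and 3 after day 42.

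| | ρ = 0.5 | ρ = 0.7 |
|---|---|---|
| Without baseline | 0.97 | 0.94 |
| With baseline | 0.74 | 0.50 |

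A closed form checks the first row. If every patient lost still had both earlier forms, the ratio would be 1 − 0.12 × 2ρ²/(1 + ρ), or 0.96 at ρ = 0.5 and 0.93 at ρ = 0.7. Staggered loss gives slightly less gain, as the table shows.

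**Loss implied by the calendar.** The Results section has enrollment from February 1, 2018 to February 28, 2020 (757 days) and results by April 30, 2020 (62 days later). Under even accrual:
- By February 28, 2020, the share short of 12 months is 365/757 = 48%, and short of 6 months 183/757 = 24%.
- By April 30, 2020, the shares are (365 − 62)/757 = 40% and (183 − 62)/757 = 16%.

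Per 50 patients, the April pattern is 30 with all forms, 12 with the first two and 8 with day 42 only. The February pattern is 26, 12 and 12, taking day 42 as complete.

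| | ρ = 0.5 | ρ = 0.7 |
|---|---|---|
| April, without baseline | 0.88 | 0.78 |
| February, without baseline | 0.85 | 0.74 |
| April, with baseline | 0.71 | 0.47 |
| February, with baseline | 0.70 | 0.46 |

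**Which contrast.** The mean of three visits has SD √((1 + 2ρ)/3), that is 0.82 to 0.89 of a single-visit SD. Suppose an effect of 0.5 SD at day 42 and none later, with 44 per arm. The averaged effect is 0.5/3 = 0.17 SD, and a t test on the visit mean has 14% to 16% power. A plain day-42 t test has 64%. With effects of 0.5, 0.25 and 0 SD, the visit mean has 25% to 30%.

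**The case against.** The strongest objection is that Statistical methods is a short generic paragraph which never mentions quality of life. A reader might infer that the plan commits to a separate test at each visit and so never compares the course over time. The text does not say that. The one value per patient could be a change score or a mean over follow-up, and a two-sample test on either would comply. This stands, so per-visit use is an inference. Still, no such summary is stated, and the method that is stated is assigned to all continuous variables.

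Second, a reader might infer a large gain in power from averaging the three visits. With a sustained 0.5 SD effect and 44 per arm, power goes from 64% to 74–81%. That figure is itself a t test on each patient's mean score, which the plan permits, so it does not show the stated test to be deficient. It also needs an effect that lasts. The objective concerns speed, and under Interventions the pump stays on only until full mobilization, so a fading effect is at least as natural. The averaged contrast then loses power.

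Third, a reader might suppose that late forms would be missing mainly from the sickest patients. The article says nothing about who fails to return forms, and a mixed model would not fully correct that kind of loss. The calendar-driven loss is better grounded, but it applies only if quality of life is analysed on the stated timetable. The abstract speaks of first results. If the 12-month forms are awaited, the loss falls back towards the planned 12%.

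Finally, modelling detail is commonly left to an analysis plan, and none is shown. That would answer a complaint about silence. Here the article names a test, and the point concerns that choice.

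**Conclusion.** The point holds as a modest improvement to a secondary objective. The stated two-sample test, used at any one visit, makes no use of baseline or other scores and excludes patients without that form. The gain from a better analysis comes mostly from baseline. At the planned 12% loss, the variance of the 12-month difference falls to about 0.74–0.50 with baseline and only to 0.97–0.94 without it. If the analysis followed the stated dates, the ratios would be about 0.71–0.46 with baseline and 0.88–0.74 without.

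These sizes rest on an assumed correlation of 0.5–0.7, on forms missing at random and, for the last pair, on even accrual. The documents do not support saying that most of the repeated information is thrown away, or that the primary result is at risk.

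**What to change.** In Statistical methods, state that VascuQol-6 and EQ-5D are each analysed with one mixed model for repeated measures. Its terms are arm, visit, arm-by-visit and baseline score (as a covariate or through a common baseline mean), with unstructured covariance within patient. Include every patient with at least one follow-up form. Report the arm difference with a 95% confidence interval at each visit, and name one main contrast in advance. Because the objective is about speed, an early visit such as day 42 suits it better than the average over visits. Keep the Wilcoxon test as a sensitivity analysis, and the two-sample tests for outcomes measured once.

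The cost is a few lines of text and a standard model command, with no new data. The downsides are an explicit missing-at-random assumption and reliance on a model for scores that may be skewed, which the sensitivity analysis addresses in part.
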